Several direct or indirect factors might be involved in the development of frailty, including low education level, depression, malnutrition, polypharmacy, low physical activity, and concomitant chronic disease [10]. The prevalence of comorbidity in frail individuals is higher than in those without frailty [4], among which, chronic kidney disease (CKD) is one of the most common diseases closely linked to frailty. Some studies found that the prevalence of frailty among patients with CKD or end-stage renal disBGR01491ease (ESRD) is 3-fold than that of patients without the disease [6]. Furthermore, frail patients undergoing hemodialysis were associated with a 2.6-fold higher risk of mortality and 1.43-fold higher risk of hospitalizations, independent of age, sex, comorbidity, and disability as compared to patients without frailty [11]. Among patients treated with peritoneal dialysis, the frail patient has a significantly high rate of death or hospitalization, as well as, prolonged duration of stay per admission [12]. Moreover, no significant difference was detected in frailty between patients with hemodialysis and peritoneal dialysis [13]. Similarly, after adjusting the recipient, donor, and other confounders, the risk of early hospital readmission and mortality of frailty patients after kidney transplantation were 1.61-fold and 2.17-fold, respectively, more than those who were non-frail [14, 15].

Several studies demonstrated that frailty could be reversed or attenuated by nutritional supplementation, cognitive training, psychological intervention, or physical exercise, and multi-domain interventions are superior to monodomain interventions, among which, exercise training plays an irreplaceable role [16]. Some investigators speculated that exercise training could ameliorate poor physical functioning and frailty. Moreover, the survival rate s in patients with CKD can be improved [17]. In the case of frail patients undergoing CKD, most investigations focus on those treated with dialysis. Currently, only a few studies have been performed in frail non-dialysis patients. Thus, the objectives of this clinical study are 1) to explore the risk factors related to frailty in elderly CKD patients without dialysis, 2) to investigate the effect of individualized interventions of frailty on the prognosis of elderly patients with CKD who did not undergo dialysis.

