### Recruitment and eligibility

Eligible subjects will be identified and recruited in the Department of Nephrology and Department of Internal Medicine Beijing Chaoyang Hospital, Capital Medical University, including outpatients and inpatients. Recruitment will be conducted through printed materials (leaflets and posters). Patients will be required to fulfill the following criteria to qualify as study participants: 1) ≥65-years-old, 2) diagnosed as CKD stage 3–5, 3) never undergone hemodialysis or peritoneal dialysis, and 4) recognized as frailty by Fried scale. Chronic Kidney Disease Epidemiology Collaboration (CKD-EPI) formula is selected to estimate the glomerular filtration rate (eGFR); eGFR< 60 mL/min/1.73 m^2^ is defined as CKD stage 3–5 [18]. The informed consents will be signed after the eligible patients agree to participate in the investigation and allow access to their data during the follow-up either by clinic or telephone contact. Patients who are 1) undergoing dialysis, 2) considered with life expectancy < 1 year such as advanced cancer patients, 3) difficult to communicate with such as patients with severe cognitive impairment (Mini Mental State Examination score ≤ 17) [19]; or severe hearing disorder will be excluded from the study.

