### Outcomes

Frailty is defined as the primary outcome to evaluate the efficiency of the personalized intervention treatment that reversed frailty to pre-frailty or non-frailty. The secondary outcomes are re-hospitalization and death that assess the effect of frailty on the prognosis of patients, medical examination such as echocardiography.

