### Statistical analysis

Participants’ demographic information, comorbidities, laboratory results, other clinical characteristics, frailty, consequences of the CGA, and outcomes at 30 days and 12 months will be presented by descriptive statistics. The measurement data in accordance with normal distribution would be described by mean values ± standard deviation, or else by median values and interquartile ranges. The enumeration data would be expressed as percentage or rate. The 95% confidence interval (CI) would be reported subsequently. To compare the differences between means, Student’s t-test will be performed, and the differences between frequencies will be compared by χ^2^ test or Fisher’s exact test. Logistic regression will be conducted to analyze the predictors of frailty and compare the groups with respect to dichotomous outcome variables. The odds ratios will represent the effect of predictors. Kaplan–Meier survival curve would be plotted, and the Cox proportional hazard regression model would assess the association between frailty and mortality. Missing data, due to loss to follow up, will be imputed using the last value carried forwards method [28]. Sensitivity analyses will be conducted to determine whether the results have been influenced by missing data. All data would be analyzed by SPSS version 23 (IBM Corp, Armonk, NY). *P*-values < 0.05 will be considered as statistically significant. All probabilities would be two-tailed.

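### The only Cox model for death takes frailty, not the randomised arm, as its exposure; with everyone frail at entry, a frail/not-frail contrast is post-randomisation and open to immortal-time bias

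*Protocol article*

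**What the plan says.** - **Objective (Background).** The second objective is "to investigate the effect of individualized interventions of frailty on the prognosis of elderly patients with CKD" not on dialysis. The first concerns risk factors for frailty. Neither asks for the association of frailty with death.
- **Outcomes.** The secondary outcomes are "re-hospitalization and death that assess the effect of frailty on the prognosis of patients", together with examinations such as echocardiography.
- **Statistical analysis, survival.** "Kaplan–Meier survival curve would be plotted", with no grouping stated, and "the Cox proportional hazard regression model would assess the association between frailty and mortality". No other time-to-event method is named.
- **Statistical analysis, yes/no outcomes.** Frequencies are compared by χ² "test or Fisher’s exact test", and logistic regression will also "compare the groups with respect to dichotomous outcome variables".
- **Eligibility.** Participants must be "recognized as frailty by Fried scale", which Measurement and procedure defines as at least three of five criteria. The same section has frailty reassessed at 30 days and 12 months.
- **Missing data.** Values missing through loss to follow-up are filled by carrying the last value forward, with sensitivity analyses. Death is not mentioned in that rule.

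**The concern.** Randomisation gives an unbiased comparison of survival between the arms, and the second objective needs that comparison. The one survival model the plan describes estimates something else: how death differs by frailty.

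A yes/no frailty variable does not vary at time zero in this trial, so the model has to borrow a state observed later. People who reverse must first survive long enough to be seen to have reversed, and they may differ in health from those who do not. The survival estimate could then suggest that reversing frailty prolongs life when it does not. A reader could take that as evidence for the intervention, although it is not a comparison of the arms.

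**Working it through.** **1. The plan's own figure.** None exists for mortality: no event rate, hazard ratio or power is given. The stated sample size concerns frailty reversal only, and it reproduces. With 25% vs 10%, two-sided α = 0.05 and 80% power, n = (1.960 + 0.842)² × (0.25×0.75 + 0.10×0.90) / 0.15² = 7.849 × 0.2775 / 0.0225 = 96.8, so 97 per group. Then 194 / 0.8 = 242.5, stated as 242.

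**2. Exposure available at time zero.** Entry requires frailty, so the yes/no variable equals 1 for everyone and a Cox model on it has no contrast. Two routes remain: the graded baseline count (3, 4 or 5 criteria), or the 30-day or 12-month reassessment, both after randomisation.

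**3. Apparent hazard ratio when reversal has no effect on death.** Inputs: reversal of 25% and 10% by arm (Design outline), averaging 17.5% under 1:1 allocation. Constant hazard and 12-month mortality of 5–30% are assumptions. The crude rates below hold for low mortality and count expected deaths per person-year, relative to the true rate.

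- *Day-30 status, clock from randomisation, early deaths kept as frail.* Reversed patients cannot die in month 1, so their rate is 11/12 = 0.917. The frail group has its own later deaths plus everyone's month-1 deaths: (0.825 × 11/12 + 1/12) / 0.825 = 0.840 / 0.825 = 1.018. The ratio is 1.018 / 0.917 = 1.11. Simulation of 400,000 patients gives 1.12–1.13.
- *Ever reversed, reversal times spread evenly over the year.* On average half the deaths among potential reversers come before reversal and are counted as frail. Reversed rate: 0.5. Frail rate: (0.825 + 0.0875) / 0.825 = 1.106. The ratio is 2.21; simulation gives 2.15–2.23.
- *12-month status, earlier deaths kept as frail.* Nobody who dies within 12 months can be classed as reversed. The simulation had 0 deaths among the reversed and all deaths among the frail, so the ratio is not estimable.
- *Day-30 landmark.* Simulation gives 1.00–1.01.

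**4. False-positive rate at n = 242 if the last observed status is the exposure.** Null simulation, two-sided log-rank test at 0.05, 17.5% reversed by 12 months, 3,000 trials per cell:

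| Reversed by day 30 (assumed) | 5% die | 10% die | 15% die |
|---|---|---|---|
| 0% | 6% | 78% | 99% |
| 5% | 2% | 30% | 51–53% |
| 10% | 1% | 11% | 19% |
| 17.5% (all) | 3% | 4% | 4% |

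A day-30 landmark keeps the rate at about 4–5%. The plan gives neither mortality nor the timing of reversal, so no single cell can be attributed to it.

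**5. What a by-arm Cox model could show.** Schoenfeld power = Φ(½ √d |ln HR| − 1.96). For HR 0.5 and overall mortality of 5/10/15%, d is about 12/24/36 deaths and power is 22/40/55%. If 5/10/15% is instead control-arm mortality, d is about 9/18/28 and power is 18/32/45%. A yes/no comparison in that second case has 17/30/42%. Power of 80% needs 66 deaths.

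**The case against.** A reader might infer more than the text supports, in four ways.

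- *That the Kaplan–Meier curve is also by frailty.* Its grouping is unstated and could be by arm. Only the Cox model is tied to frailty.
- *That the effect of the intervention on death is not estimated.* It is: logistic regression and χ² or Fisher tests compare the groups on dichotomous outcomes, and death by a fixed 12 months is one. Their power is close to that of a Cox model. Only the time-to-event comparison by arm is absent.
- *That the planned hazard ratio will be biased.* The article does not say which frailty measurement enters the model or how. A landmark, a correctly coded time-dependent covariate or the baseline count carries no immortal-time bias, and a condensed article may leave that coding to a fuller plan.
- *That deaths are assigned the last frailty state.* Carry-forward is stated only for loss to follow-up.

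It can also be said that studying an association is a legitimate observational aim, and that death is an unsized secondary outcome. All of this stands, and it limits the size of the point. It does not remove the mismatch: two sections name frailty as the exposure where the objective names the intervention. A fuller plan would have to depart from those sentences, not just add detail. The yes/no comparison also leaves a question of validity. With 20% loss planned (0.20 × 242 ≈ 48 people), carrying the last value forward for death, read literally, counts those lost while alive as alive at 12 months.

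**Conclusion.** The point holds in limited form. The only stated Cox model does not address the second objective, no time-to-event comparison by arm is stated, and any frail/not-frail contrast is non-randomised because entry requires frailty.

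Immortal-time bias is conditional on entering post-randomisation status as fixed from time zero. It is then small with day-30 status (hazard ratio about 1.12 under no effect) and extreme with 12-month status. It is also severe with last-carried status when few have reversed by day 30. It is absent with a landmark, time-dependent or baseline-count model, although those remain observational.

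The day-30 and 12-month results vary little over the assumed mortality of 5–30%. The false-positive rates depend strongly on assumed mortality and on the timing of reversal. The primary outcome and sample size are unaffected. This should be fixed, but it does not undermine the trial.

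**What to change.** - **Statistical analysis.** Make the randomised arm the exposure for the Kaplan–Meier curves and for a Cox model of time from randomisation to death. Analyse all 242 as allocated. Censor participants lost to follow-up at last contact, and do not carry them forward as alive.
- **Outcomes.** State that death and re-hospitalisation assess the effect of the intervention.
- **Frailty–mortality model, if kept.** Label it exploratory and observational. Use day-30 status in a landmark analysis of those alive at day 30, frailty as a time-dependent covariate, or the baseline Fried count. Do not treat 12-month or last-carried status as a baseline exposure.

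**Cost.** Mostly wording, but not only that. The article attaches a time to re-hospitalisation, not clearly to death, and does not mention last-contact dates. Both dates must be recorded. The gain is in the validity of the comparison and the handling of losses, not in power. The plan should say openly that the by-arm hazard ratio will be imprecise (about 20–55% power for a hazard ratio of 0.5 at an assumed 5–15% mortality).

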## Methods

### Design outline

A single center randomized parallel controlled trial with a follow-up period of 30 days and 12 months will be conducted. According to our pretest data, the reversion of frailty approached 25% in intervention group while 10% in control group, a total of 97 frail subjects are needed in each group (*α* = 0.05; *β* = 0.2; two-sided contrast). Considered a lost to follow-up rate of 20%, increased the sample size to 242. And, referring to relevant literatures, the frailty was reversed by individualized intervention, ratio is approaching 35 and 15% for the frailty versus non-frailty [16]. 71 patients for per group will be needed (*α* = 0.05; *β* = 0.2; two-sided contrast). Taking into account a rate of 20% loss to follow-up, increased the sample size to 178. Finally, the whole sample size is 242 in order to get the higher statistical power. All eligible participants will be randomized (1:1 allocation ratio) into control and intervention groups, and the latter would receive individualized interventions according to the consequence of the comprehensive geriatric assessment (CGA). The outcome data would be collected at baseline, 30 days, and 12 months (Fig. 1, Table 1).

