### Measurement and procedure

Frailty will be identified using Fried [20], including 5 components: 1) Shrinking, unintentional weight loss ≥10 pounds in last years or ≥ 5% of body weight in the previous year. 2) Weakness, based on grip strength, stratified by gender and body mass index (BMI) quartiles. For men, BMI ≤24 kg/m^2^, grip strength ≤29 kg; BMI 24.1–26 kg/m^2^, grip strength ≤30 kg; BMI 26.1–28 kg/m^2^, grip strength ≤30 kg; BMI > 28 kg/m^2^, grip strength ≤32 kg. For women, BMI ≤23 kg/m^2^, grip strength ≤17 kg; BMI 23.1–26 kg/m^2^, grip strength ≤17.3 kg; BMI 26.1–29 kg/m^2^, grip strength ≤18 kg; BMI > 29 kg/m^2^, grip strength ≤21 kg. In this study, we will measure the grip strength of the dominant hand twice to obtain the average. 3) Exhaustion, self-reported fatigue ≥3 days in the last week. 4) Low activity level, energy expenditure of physical activity per week < 383 kcal for men or < 270 kcal for women. 5) Slow gait speed, based on the time required for walking 15 ft. Walk time ≥ 7 s for men with ≤173 cm height or women with ≤159 cm height or walk time ≥ 6 s for men whose height was > 173 cm or women whose height was > 159 cm was considered as slowness. The presence of ≥3 criteria is defined as frailty, 1 or 2 is classified as pre-frailty, and 0 is regarded as non-frailty.

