Participants with two or more problems will be treated simultaneously by the relevant specialists. Furthermore, the intervention group was subjected to the management of chronic disease and assessment of medication for rational use of medicine, which will be accomplished by geriatric doctors mainly. Discontinuation of the intervention may occur in case of health decline or if a participant wishes to stop taking part in the intervention group. Communication and encouragement will be used to improve adherence to intervention. Reasons and information for drop outs will be documented.

All participants will be followed up for 30 days and 12 months through clinic or telephone contact by specific personnel who are blinded to group allocation to minimize the bias. The content of follow-up will include frailty reassessment using frailty phenotype, frequency, time, main medical conditions of rehospitalization, death and echocardiography.

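### Carrying the last value forward fixes the 12-month frailty result of everyone lost to follow-up at their baseline or 30-day state, which can bias the comparison in either direction

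*Protocol article*

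**What the plan says.** Under Statistical analysis, the protocol article gives one rule: "Missing data, due to loss to follow up, will be imputed using the last value carried forwards method". It continues: "Sensitivity analyses will be conducted to determine whether the results have been influenced by missing data". No method or alternative assumption is given for those analyses.

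Four other statements determine what the rule does here:

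- **Entry state.** Recruitment and eligibility requires each participant to be "recognized as frailty by Fried scale", so everyone starts frail.
- **Definition.** Measurement and procedure: "The presence of ≥3 criteria is defined as frailty, 1 or 2 is classified as pre-frailty, and 0 is regarded as non-frailty".
- **Primary outcome.** Outcomes: "Frailty is defined as the primary outcome to evaluate the efficiency of the personalized intervention treatment that reversed frailty to pre-frailty or non-frailty". This is a yes/no result, and the section does not say whether 30 days or 12 months is the primary time point.
- **Visits and expected loss.** Design outline: "The outcome data would be collected at baseline, 30 days, and 12 months", and "Considered a lost to follow-up rate of 20%, increased the sample size to 242".

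**The concern.** Carrying a value forward assumes that the state does not change after a person leaves. That fits this design poorly. The outcome is a change of state, the Background ties frailty to later disability, hospitalization and death, and the exercise programme runs for 12 months. With one intermediate visit, only two values can be carried:

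- **Lost before day 30:** the baseline state is carried. It is always frail, so the result is always not reversed.
- **Lost after day 30:** the 30-day state stands as the 12-month result. An early reversal that did not last counts as a success, and a reversal that came later counts as a failure.

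What is at stake is the 12-month difference in reversal. Depending on the timing of loss and its balance between arms, the rule can shrink a real effect, create an apparent effect where there is none, or enlarge a real one. It cannot be called conservative in advance.

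**Working it through.** **Inputs from the protocol article (Design outline).** Reversal 25% vs 10%; two-sided α = 0.05; β = 0.2; 97 per group before loss; 20% loss; 242 in total; 1:1 allocation, so 121 per arm.

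**Inputs assumed.** Timing of loss, balance of loss between arms and 30-day reversal rates. The article gives none of these, so several values are shown.

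**Step 1. The plan's own figure.** Unpooled two-proportion formula:

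n = (1.960 + 0.842)² × (0.25×0.75 + 0.10×0.90) / 0.15² = 96.8, so 97 per group. For loss, 194 / 0.8 = 242.5, against 242 stated. The figure reproduces.

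**Step 2. How many values are carried.** 0.20 × 121 = 24.2 per arm. The planned difference is 0.15 × 121 = 18.2 reversals per arm, so the imputed values outnumber the effect sought.

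**Step 3. What the rule yields.** Let p be the 12-month reversal rate in an arm, d its loss, f the share of that loss occurring before day 30, and r the 30-day reversal rate among those lost later. Then

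rate after carrying forward = (1 − d)·p + d·(1 − f)·r

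It is assumed throughout that those lost would have had the same 12-month rate p as those who stayed. Rejection and power use the two-proportion normal approximation with 121 per arm and pooled variance under the null.

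| Assumed situation | True 12-month rates | After carrying forward | Power or rejection |
|---|---|---|---|
| A. 20% lost in each arm, all before day 30 | 25% vs 10% | 20% vs 8% | power 77.1% |
| B. No effect, equal 20% early loss | 10% vs 10% | 8% vs 8% | rejection 5% |
| C. No effect, early loss 30% vs 10% | 10% vs 10% | 7% vs 9% | rejection 8.8% |
| C. As above | 17.5% vs 17.5% | 12.25% vs 15.75% | rejection 12.3% |
| C. As above | 25% vs 25% | 17.5% vs 22.5% | rejection 16.3% |
| D. No effect, 20% lost after day 30, 30-day rates 25% vs 10% | 10% vs 10% | 13% vs 10% | rejection 11.3% |
| D. As above, 30-day rates 40% vs 10% | 10% vs 10% | 16% vs 10% | rejection 28.3% |
| E. 20% lost after day 30, 30-day rates 5% vs 5% | 25% vs 10% | 21% vs 9% | power 74.6% |
| E. 20% lost after day 30, 30-day rates 35% vs 10% | 25% vs 10% | 27% vs 10% | power 93.1% |

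Examples: in A, 0.8×0.25 = 0.20 and 0.8×0.10 = 0.08. In the first D row, 0.8×0.10 + 0.2×0.25 = 0.13 against 0.8×0.10 + 0.2×0.10 = 0.10.

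**Step 4. Power on a like-for-like basis.** Compare 97 completers per arm at 25% vs 10% with 121 per arm at 20% vs 8%, using the same formula for both. Pooled: 79.0% falls to 77.1%. Unpooled: 80.1% falls to 78.0%. Equal early loss costs about 2 points.

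**Step 5. Standard error of the difference in situation A.** √[(0.20×0.80 + 0.08×0.92)/121] = 0.044. With 97 observed per arm at 25% vs 10% it is √[(0.1875 + 0.09)/97] = 0.053. These belong to different target differences (12 and 15 points), so the contrast does not by itself show an interval that is too narrow.

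**The case against.** The best defence is that little need go wrong. With equal early loss the rule amounts to scoring missing as not reversed: the test keeps its 5% level and power drops by about 2 points. The false-positive results need unequal loss, or a transient 30-day effect with loss concentrated after day 30, and the article supplies neither. The late-loss mechanism also disappears if the primary comparison is at 30 days. Sensitivity analyses are promised, and their detail may be in a document not shown.

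Most of this stands as a limit on size and severity. It does not rescue the rule, which is stated, is the only one named, and decides about a fifth of the 12-month results. An unspecified sensitivity analysis leaves the headline estimate unchanged.

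A reader might infer more than the article supports:

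- **That the planned 80% power is not delivered.** Setting 77% against 80% mixes two formulas (step 4), and late loss can raise power to 93%.
- **That the sample size does not match the analysis.** Inflating 97 per group for 20% loss is ordinary practice and reproduces. Later analysing all 121 does not contradict it.
- **That the interval is generally too narrow.** Step 5 does not establish this.
- **That deaths are carried forward as successes.** The rule covers loss to follow-up only. The article is silent on frailty status after death, which is an omission and not a stated error.
- **That people who decline are counted as reversed.** "Discontinuation of the intervention may occur in case of health decline" concerns stopping the intervention, not leaving follow-up. It would happen only to someone who had reversed at day 30 and was then not assessed at 12 months.

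**Conclusion.** The concern holds for the 12-month frailty comparison. The only named imputation rule assigns about 24 of 121 results per arm from a state recorded at entry or at day 30, and the resulting bias has no fixed direction. Under the assumptions shown, equal early loss does no more than dilute the effect from 15 to 12 points. With no true effect, unequal early loss of 30% vs 10% gives 9% to 16% rejection, and a transient 25% vs 10% effect followed by 20% late loss gives about 11%. Late loss can also enlarge a real effect, from 15 to 17 points in the example.

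These sizes rest on assumed timing, balance and 30-day rates. They show what the rule can do, not what will happen. Severity: should-fix.

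**What to change.** For the 12-month frailty comparison:

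1. Replace last value carried forward with multiple imputation, done separately by arm, using baseline Fried count, 30-day Fried components, age, eGFR and baseline SPPB.
2. In the same analysis, treat death before 12 months as not reversed and do not impute it.
3. Name a tipping-point analysis, varying the reversal rate among the missing by arm, as one of the promised sensitivity analyses.
4. Keep last value carried forward only as a further sensitivity analysis.

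The cost is a change of wording and modest programming before database lock, and possibly a wider confidence interval. All the variables are already in the article's baseline or follow-up assessments, so no new data are needed.
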